Primary outcomes will include the following clinical measures: Assisting Hand Assessment (AHA), Box and Block Test (BBT), and performance at the Visuomotor task. Secondary outcomes will include the scores at the following tests: Children’s Hand Experience Questionnaire (CHEQ), Canadian Occupational Performance Measure (COPM), Gross Motor Function Measure (GMFM-66); Melbourne Assessment-2 (MA2) scale, Vineland Adaptive Behavior Scale Version 2 (VABS II), and Pediatric Quality of Life Inventory (PEDS-QL). Vital parameters (i.e., oxygen saturation, SpO2, and Heart Rate, HR) and the scores at the questionnaires assessing stimulation-induced sensations will be also checked to assess the safety and the tolerability of the stimulation. Lastly, the feasibility and the acceptability of the training will be assessed by considering, respectively, the number of patients completing the training/the number of sessions for each patient and the response to *ad-hoc* questionnaires for the patients and their parents. All primary and secondary outcomes will be collected at each time point, except for the PEDS-QL and VABS II, which will be administered only at T0 and T2. Furthermore, vital cardiovascular parameters and the questionnaires assessing stimulation-induced sensations will be examined during each stimulation session. The acceptability questionnaires will be administered only after the end of the training (T1) (see Figure 1).

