## Outcome measures

The primary outcomes consist of two validated measures of manual dexterity, namely the Assisting Hand Assessment (AHA), and the Box and Block test (BBT), and a pc-administered, *ad-hoc* visuomotor task for the evaluation of manual visuomotor control. Secondary outcomes encompass a comprehensive assessment of motor skills, functional adaptation, and quality of life. The following paragraphs provide a detailed description of both primary and secondary outcomes (Figure 2).

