### Primary outcomes

#### Assisting hand assessment

This scale enables quantifying the assistance provided by the more affected hand to the less affected hand during bimanual activities. This observation-based, criterion-referenced assessment highlights a person’s typical performance, emphasizing practical functionality over maximal capacity, and serves as a reliable measure of change over time. The scale comprises 20 items, scored on a four-point Likert scale, from 1 to 4. The total score indicates how well the more affected hand is used as an assisting hand. A score of 20 means poor performance (the hand is not used as an assisting hand); a score of 80 means that the hand is used effectively. The results are converted for each of the three scales to logits by a Rasch analysis, on a 0–100 scale (with higher scores suggesting better use). This assessment has been shown to be responsive, reliable and valid for use in children with CP (38).

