#### The box and block

This test is designed to measure manual dexterity. It is quick, simple, and cost-effective. It involves a box with a partition in the middle placed on a table, with a total of 150 blocks on one side of the partition. The score of the test is given by the number of blocks transported within a minute (39, 40) and it is performed with both the less and the more affected hands. The BBT provides a reliable and objective measurement of manual dexterity, making it valuable for evaluating functional outcomes and monitoring progress in rehabilitation programs over a short period of time (41).

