#### The visuomotor task

This is an *ad hoc* computer-based task for the evaluation of manual visuomotor control. It involves a mouse click-and-drag operation where an object appears at the center of the screen. The objective is to drag and drop the object to the location indicated by a previously presented arrow, pointing toward a target object within a configuration of objects. Participants are required to focus on the direction of the arrow, swiftly and accurately moving the central object to its designated target location, by using a mouse with the less affected hand. This task enables the measurement of movement time (MT, in milliseconds; consisting in the time necessary to move the object in the target position); precision error (calculated as the distance, in pixels between the drop position of the object and the actual target position); the proportion of overtime errors (the percentage of trials in which responses are too slow). Smaller values of Movement time, Precision error and overtime errors indicate better performance.

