## Statistical analysis

Statistical analyses will be performed using STATISTICA 8.0 (StatSoftInc, Tulsa, Oklahoma). Demographic and clinical variables of the two groups of patients will be inspected through descriptive statistics. Independent sample *t*-test (two-tailed) and χ^2^ will be used to assess the differences between the experimental and control training groups at baseline for continuous and categorical variables, respectively, thus allowing us to verify successful randomization. The outcome measure data will undergo a normal distribution assessment using Kolmogorov–Smirnov tests. If the data adheres to a normal distribution, repeated measures ANOVAs will be employed to analyze differences between treatment group (active vs. sham) and across timepoints (T0-T1-T2) on the primary and secondary outcomes. Duncan *post hoc* tests will be performed to follow-up significant interactions and correct for multiple pair-wise comparisons. Conversely, for data not following a normal distribution, the Kruskal-Wallis H test or Friedman test will be applied. The exploratory analysis will center on investigating sex and age differences in treatment response, considering both primary and secondary outcomes. Furthermore, in light of findings on hemisphere-specific tVNS effects cortical excitability (20) and electrophysiological readiness potentials (52), we will conduct a sensitivity analysis. This analysis will examine potential differences in tVNS effects when administered ipsilateral or contralateral to the side of the most affected limb. Statistical significance will be denoted by *p* < 0.05. As to what concerns missing data, a modified intention-to-treat analysis approach will be adopted, including in the analyses all the participants who had completed the pre- and post-treatment evaluation sessions, even if they had not completed all the training sessions. No imputation of missing data, however, will be used considering the limited sample size and observation points.

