## Discussion

Task-specific training, which are goal and functional oriented, are the most promising approach for the treatment of CP (9). Though, available evidence suggested that the effectiveness of these interventions decreases as the children grow (3). Thus, there is an urgent need to identify the most effective rehabilitation approaches that confer the greatest clinical gain, not only in the youngest, often “over-treated” children, but also in more chronic conditions, as for older children and adolescents with CP, using new forms of intervention that may adjuvate the rehabilitation by boosting brain plasticity.

The current trial aims at filling this gap, by proposing a protocol that can be individualized on patients’ needs and that will exploit neural plasticity as induced by tVNS. In this trial, 6–17 years old aged patients with unilateral or bilateral CP will be treated in pairs, with a matching of motor deficit severity, IQ, or age. Each pair will be randomly assigned to the active or to the sham tVNS group. During the application of the active or sham tVNS protocol, both groups will undergo a bimanual training according to the Habit-ILE protocol, which train bimanual tasks, including recreational play activities, while systematically engaging postural control of the trunk and lower limbs in an ecological and highly motivating environment. Training activities will be carried out for 2 consecutive weeks, 5 days per week, for 3 h/day, with an overall dose of 30 h of intervention. TVNS will be applied for the first 75 min in each session. As primary outcome measures, we will quantify the improvements in manual visuomotor control. Secondary outcomes will instead encompass a comprehensive assessment of motor skills, functional adaptation, and quality of life. Safety and tolerability will be evaluated too.

The study design provides for an active control group that will receive sham tVNS during participation to the training, thus accessing a treatment that represents the gold standard for CP. The comparison between the two groups will allow us to test the specific, modulatory effects on tVNS on the changes induced by the training. At the same time, it will allow us to test the transferability into everyday life adaptive behavior and quality of life.

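### Three primary outcomes are each tested at p < 0.05 with no correction across them and no success rule, while the sample size covers one test at 0.05

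*Protocol article*

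**What the plan says.** The Design section sets the primary family: "Primary outcomes will include the following clinical measures: Assisting Hand Assessment (AHA), Box and Block Test (BBT), and performance at the Visuomotor task". The Abstract and the Outcome measures section list the same three instruments.

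The descriptions of the individual measures give more than one score for two of them:
- **Assisting Hand Assessment (AHA):** one total. "The total score indicates how well the more affected hand is used as an assisting hand".
- **Box and Block Test (BBT):** "it is performed with both the less and the more affected hands". Neither hand is named as the primary score.
- **Visuomotor task:** done "by using a mouse with the less affected hand", with three measures. "Smaller values of Movement time, Precision error and overtime errors indicate better performance". None of the three is named as the primary score.

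The Statistical analysis section plans repeated-measures ANOVAs (group by T0, T1, T2) on the primary and secondary outcomes. It sets one threshold: "Statistical significance will be denoted by" p < 0.05. Duncan post hoc tests follow a significant interaction and are meant to correct the pair-wise comparisons.

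The Sample size calculation section gives 22 per group for power 0.80 at alpha 0.05, with f(U) = 0.35 and 2 numerator degrees of freedom.

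The Discussion says: "As primary outcome measures, we will quantify the improvements in manual visuomotor control". In the Outcome measures section that label belongs to one instrument, the "visuomotor task for the evaluation of manual visuomotor control".

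**The concern.** With three primary outcomes, the trial's claim depends on a rule for combining them: any one, a set number, or all. The article gives none. It does fix a 0.05 threshold for every test, limits the stated correction to comparisons within one ANOVA, and powers one test at 0.05.

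That combination does not fit either natural success rule. If one positive outcome is enough, the 5% error rate does not hold for the trial's claim. If all three are needed, the stated power does not hold for it.

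The Discussion adds uncertainty about what the primary claim is. It keeps the visuomotor task, done with the less affected hand, and leaves out AHA, which scores the more affected hand as an assisting hand. Results on the two could differ, so the sections must agree.

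**Working it through.** **Inputs.** From the Sample size calculation section: N = 44 (22 per group), f(U) = 0.35 with the SPSS option, three time points, numerator df 2, alpha 0.05, power 0.80. From the Design section: three primary instruments. From the measure descriptions: up to 1 + 2 + 3 = 6 scores. The documents give no correlation between outcomes, so it is an assumption and a range is shown.

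**Step 1. Reproduce the stated power.** For the group-by-time interaction under sphericity:

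λ = f² × (N − 2) × (3 − 1) = 0.1225 × 42 × 2 = 10.29, with F on 2 and 84 df.

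Power at alpha 0.05 is 0.812 with N = 44 and 0.791 with N = 42. So 44 is the smallest even N that reaches 0.80. The sample size is right for one test.

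**Step 2. Any one positive primary counts.** Count one interaction test per outcome. For independent tests:
- three outcomes: 1 − 0.95³ = 0.143
- six scores: 1 − 0.95⁶ = 0.265

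For correlated outcomes, interaction F tests were simulated with N = 44, equal correlation between outcomes and 40,000 runs per setting:

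| Assumed correlation | Three outcomes | Six scores |
|---|---|---|
| 0 (exact) | 14.3% | 26.5% |
| 0.3 | 13.6% | 24.4% |
| 0.5 | 12.7% | 21.0% |
| 0.7 | 11.4% | 16.7% |
| 0.9 | 8.4% | 11.4% |

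For the three named outcomes this is 1.7 to 2.9 times the nominal 5%.

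**Step 3. All three must be positive.** The family-wise error rate is then no higher than 5%. Joint power cannot exceed the single-test 0.812, and reaches it only if the outcomes move together perfectly. With independent outcomes, each with f(U) = 0.35, it is 0.812³ = 0.54.

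**Step 4. Correct across outcomes.** With the same λ and df:
- three outcomes, first step 0.05/3 = 0.0167: power 0.67; N = 56 is needed for 0.80
- six scores, 0.05/6 = 0.0083: power 0.57; N = 64 is needed for 0.80
- one named primary score at 0.05: power stays at 0.81 with N = 44

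Holm rejects whatever Bonferroni rejects and sometimes more. So 0.67 is a minimum for each outcome that has the assumed effect.

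**The case against.** The strongest reply is that this is a condensed article and a separate analysis plan may exist. The success rule, the procedure across outcomes, the BBT hand and the visuomotor summary score could all be settled there. For the choice of score within an instrument, that is fair. It does not dispose of the point, because the article itself states the threshold, the scope of the correction and power for one test at 0.05. A later plan that corrected across outcomes would no longer match that power statement.

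Three stronger readings are tempting, and the documents do not support them:

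- **Any one of six scores can be claimed as a positive primary, so the error rate is several times 5%.** The article names three primaries. Its BBT text describes how the test is given, and both hands are needed anyway for the 25% eligibility difference in Patient selection. The visuomotor text lists what the task can measure. Six primary tests is a possible reading and is not stated. Nor does the article say that one positive result is enough.
- **The Discussion names a different primary.** It names a subset of the declared primaries. That is a wording conflict, and it does not cause the inflation.
- **AHA ought to be the sole primary.** The authors note in the Discussion that AHA was developed for unilateral deficits, while bilateral cases are admitted here. Which measure leads is the investigators' choice.

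**Conclusion.** The point holds for the three named primaries. As written, the plan does not keep 5% for the primary claim if any one positive outcome is enough: the chance of at least one false positive is about 14% for independent tests, 13% at a correlation of 0.5 and 8% at 0.9. The range of 11% to 26% applies only if both BBT hands and all three visuomotor scores are also tested as primaries. If all three outcomes must be positive, alpha holds and the shortfall is in power for the joint claim, which is below 0.80 unless the outcomes are almost perfectly correlated.

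These figures rest on one interaction test per outcome, sphericity, equal correlation between outcomes (assumed) and, for power, f(U) = 0.35 on each outcome. The sample size calculation is correct for the single test that it describes. The Discussion sentence is a separate inconsistency to put right.

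**What to change.** Before unblinding, choose one of two routes and state it in the protocol and the registration:

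1. **Keep three primaries.** Name one score per instrument (for BBT, which hand; for the visuomotor task, which measure). Apply Holm across the three, and restate power as at least 0.67 per outcome at the 0.0167 first step, with N = 44 and f(U) = 0.35.
2. **Name one primary score at 0.05**, chosen by the investigators. The stated power (0.81) then stands. Test one named score from each of the other two instruments in fixed order as key secondary outcomes.

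In either case, change the Discussion sentence so that it lists the same primary outcomes as the Design and Outcome measures sections.

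The cost is lower stated power under the first route, or loss of primary status for two measures under the second. Both are changes of wording and need no new data.

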**Figure 1 fig1:**
[figure not shown]
Flow chart of patient’s inclusion and experimental procedures. ^*^The PedsQL and VABS-II will be administered only at T0 and T2, while all other measures will be administered at all timepoints.

Each pair of patients will be randomly assigned to one of two groups (active vs. sham group) with an allocation ratio 1:1, through a computer-generated blocked randomization procedure conducted by independent personnel not directly involved in performing the intensive training. The patients and their parents, the personnel responsible for conducting the bimanual training and analyzing clinical data will be kept blind to the group allocation. Instead, the coordinator of the study and the personnel administering the tVNS will be “not blind.” With respect to the clinical assessment, the staff administering and scoring the scales will be blinded to group allocation. Questionnaire scores and neuropsychological tests will not contain personal information about the patients, who will be identified by an alphanumeric code. All records that contain names or other personal identifiers, such as informed consent forms, will be stored separately from study records identified by code number. In order to uphold the overall quality and credibility of the clinical trial, instances of code breaks should be limited to exceptional circumstances, where knowledge of the actual treatment is deemed absolutely necessary for the ongoing management of the patient. The intensive treatment will take place at the Scientific Institute, IRCCS E. Medea in Bosisio Parini (Lecco, Italy; study sponsor), Fondazione Mondino IRCCS in Pavia (Italy), and ASST Ospedali Civili in Brescia (Italy). The SPIRIT checklist used for protocol reporting can found in the Supplementary material.

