
## Sample size calculation

Using the GPower 3 software (51) with the “as in SPSS option” we estimated that, with a mixed design comprising the between group factor (active group vs. sham group) and the within variable (Pre T0-, post T1-, follow-up T2, numerator DF = 2), a sample of 22 subjects per group allows detecting, with a power of 0.80 and an alpha level set at 0.05, a between group difference between active and sham tVNS combined motor training of moderate to large effect size [f (U) = 0.35], which is expected to lead to a clinically-relevant improvement in motor activity and dexterity.

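### PedsQL and VABS-II are measured only at T0 and T2, but the analysis section gives them a three-visit model and an entry rule that depends on T1

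*Protocol article*

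**What the plan says.** The Design section lists six secondary instruments: CHEQ, COPM, GMFM-66, Melbourne Assessment-2, VABS-II and PedsQL. All outcomes are collected at every visit "except for the PEDS-QL and VABS II, which will be administered only at T0 and T2". The Figure 1 legend repeats the schedule: "The PedsQL and VABS-II will be administered only at T0 and T2, while all other measures will be administered at all timepoints".

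The Statistical analysis section prescribes, for normally distributed data, repeated-measures ANOVAs comparing active with sham "across timepoints (T0-T1-T2) on the primary and secondary outcomes". No outcome is exempted. If normality fails, "for data not following a normal distribution, the Kruskal-Wallis H test or Friedman test will be applied"; no visits are named for that route. The analysis set is called modified intention-to-treat, "including in the analyses all the participants who had completed the pre- and post-treatment evaluation sessions", and missing values are not imputed.

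The Sample size calculation section fixes what the visit labels mean: "Pre T0-, post T1-, follow-up T2, numerator DF = 2". The abstract uses the same labels. The post-treatment session is therefore T1, and T2 is the follow-up.

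The Discussion says of the comparison between arms that "it will allow us to test the transferability into everyday life adaptive behavior and quality of life".

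**The concern.** The schedule makes an exception for two outcomes, and the analysis section does not take it up. This has two consequences.

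First, the stated time factor has three levels, but these outcomes have two. Someone following the text must decide how to adapt the model: a two-level ANOVA, a change score, or T2 adjusted for T0. The text does not choose, so the choice could be made after the data are seen.

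Second, entry to the analysis depends on attending T1, which has no bearing on whether a child has PedsQL or VABS-II data. Complete pairs of values could be dropped from a trial of 44 because of a missed visit at which these scales were never due.

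The two scales are the plan's dedicated measures of adaptive behaviour and health-related quality of life, the constructs named in the Discussion's statement on transfer to everyday life.

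**Working it through.** **Model against schedule.** The stated factor is time at T0, T1, T2. The values that exist for PedsQL and VABS-II are at T0 and T2. One level is empty for every child by design, so the three-level model cannot be fitted to them. With the empty level removed, the group-by-time interaction has 1 numerator degree of freedom. It is then the square of the two-sample t test on the change from T0 to T2. A valid comparison of the arms can therefore be recovered, but it is not the one written.

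**Entry rule against schedule.** The possible attendance patterns for a child with a T0 assessment are:

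| T1 attended | T2 attended | In the stated set (T0 and T1) | Has a T0-T2 pair on PedsQL and VABS-II |
|---|---|---|---|
| yes | yes | yes | yes |
| yes | no | yes | no |
| no | yes | **no** | **yes** |
| no | no | no | no |

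The rule and the data disagree in rows two and three. In row two the child is in the set but, without imputation, adds no T0-T2 change; no choice of analysis set recovers that value. In row three a complete pair is discarded. Only row three is an avoidable loss.

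**Size.** Two of six secondary instruments are affected. Each row-three child is 1/44 = 2.3% of the planned sample on both scales. The documents give no missed-visit rate, so the number of such children cannot be estimated.

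**The plan's own sample size figure.** Inputs from the Sample size calculation section: N = 44 in k = 2 groups, m = 3 visits, f(U) = 0.35, alpha 0.05, the SPSS-type effect size option. Sphericity is assumed, and children are treated as independent.

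- Formulas: df1 = (k − 1)(m − 1); df2 = (N − k)(m − 1); noncentrality λ = f(U)² × (N − k) × (m − 1).
- Three visits: df1 = 2; df2 = 42 × 2 = 84; λ = 0.1225 × 42 × 2 = 10.29; power 0.812. This agrees with the stated 0.80.
- Two visits, same f(U): df1 = 1; df2 = 42; λ = 0.1225 × 42 = 5.145; power 0.601.

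The stated sample size thus reproduces for outcomes measured at three visits and does not carry over to PedsQL or VABS-II. This is context only, because the plan claims no power for these two outcomes.

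**Choice of two-visit analysis.** With equal variances at T0 and T2 and correlation ρ between them (not given in the documents), the variance of the arm comparison is proportional to 2(1 − ρ) for change scores and to 1 − ρ² for T2 adjusted for T0. The ratio of the second to the first is (1 + ρ)/2, which never exceeds 1. Adjustment therefore costs no precision beyond the one degree of freedom for the covariate, and it uses a T0 score already collected.

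**The case against.** The strongest reply is that this is a lapse of drafting. The two-visit schedule is stated twice, so a reader of the whole article knows which time levels exist. The group-by-time ANOVA reduces naturally to T0 and T2 and gives a valid test. The non-parametric route names no visits and so does not conflict with the schedule. T1 falls 1 or 2 days after training ends, and nothing suggests that children will miss it and then return at three months. Everyday function is also covered by CHEQ and COPM, both collected at T1. Finally, a journal article condenses, and details for each endpoint may sit in an analysis plan that is not shown.

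Most of this stands, and it limits the size of the point. A reader might infer that these two outcomes are left with no analysis, or that they are analysed in the wrong population. The documents support neither. A two-level analysis is recoverable, and the stated set differs from the right one only for children who attend exactly one of T1 and T2. The child with T1 but no T2 is also no special defect here: the missing-data rule leaves that child's record incomplete on every outcome.

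Two things are not answered. The article does not merely omit a detail: it states a model, the outcomes it covers and an entry rule, and these conflict with its own schedule. And reducing the time factor to two levels does not repair the entry rule, which still excludes a child with complete T0 and T2 values. Nor does the non-parametric route settle the comparison, since a Friedman test over T0 and T2 tests change over time and not active against sham.

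**Conclusion.** The point holds as a minor inconsistency. As written, the three-visit model cannot be fitted to PedsQL and VABS-II, and the analysis set for them is conditioned on a visit at which neither is collected. The avoidable loss is confined to children seen at T0 and T2 but not at T1. Their number is unknown and may be zero.

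The primary outcomes (AHA, Box and Block Test, visuomotor task) are collected at all three visits and are unaffected, as is the sample size.

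The conclusion rests on reading the post-treatment session as T1, which the abstract and the Sample size calculation section both support, and on taking the analysis section's reference to primary and secondary outcomes as covering all of them, since it names no exception.

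**What to change.** In the Statistical analysis section:

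1. For PedsQL and VABS-II, state that the T2 score is compared between arms with the T0 score as covariate, in every randomised child with T0 and T2 values, whether or not T1 was attended.
2. Limit the T0-T1-T2 model and the T0-plus-T1 entry rule to outcomes collected at T1.

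A two-level T0-T2 ANOVA in the same children would also remove the contradiction. Adjusting for T0 is preferable because it is at least as precise apart from the one degree of freedom, and it needs no new data.

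The cost is two sentences. The number analysed may differ slightly between outcomes and should be reported for each.

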## Design

This clinical trial represents one of the two Randomized Clinical Trials (RCT) of the project “Bottom-up and tOp-down neuromOdulation of motor plaSTicity in cerebral palsy” (BOOST; FRRB 3438840). The study is a randomized, double-blind, sham-controlled pre-post-test study involving 44 children and adolescents with CP. Patients will be treated in pairs, with a matching of motor deficit severity, IQ, or age, by meeting at least two out of these three criteria. Motor severity will be defined on the basis of the Manual Ability Classification System (MACS) level and classified as low to middle (I-II level) or as middle to high (II-III). With respect to age, two group levels will be identified for children (from 6 to 11 years old patients) and adolescents (12–17 years old patients). With respect to IQ, low IQ value (from 50 to 70) and high IQ value (> 71) will be distinguished. Each pair will be randomly assigned to the active or to the sham tVNS group. The randomization will be stratified based on IQ, MACS level, or age. As for the matching within each pair, at least two out of these three criteria must be encountered.

Both groups will undergo a bimanual training in an ecological and highly motivating environment while carrying out bimanual tasks, including recreational play activities during the application of the tVNS protocol. During the training, starting from a set of proposals the choice of the type of activities to be practiced in each session will be left to patients, boosting the motivational aspect of the training. This will also ensure an individualized and goal-directed approach. The therapists will monitor and modify the activities within each pair to ensure that the intervention maintains the quality of the individualized intervention. The positions performed during bimanual tasks and the activities of daily living will be designed to systematically engage postural control of the trunk and lower limbs according to Habit-ILE protocol. The training will be carried out by a therapist with expertise in maintaining the 1:2 ratios. Training activities will be carried out for 5 consecutive days for 3 h/day for 2 weeks (30 h of intervention overall). Children and adolescents will be assessed 1 or 2 days before the start of the treatment (T0), 1 or 2 days after the end of the treatment (T1), and at a follow-up after 3 months (T2).

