### Feasibility and acceptability of the training

Feasibility of the training will be assessed by considering (i) the number of patients who complete the 2-week training and (ii) the number of sessions completed per patient. These values, expressed as percentage and mean percentage will be extrapolated at T1. Higher values will indicate higher feasibility. Lastly, the acceptability will be assessed by asking the child/adolescent and his/her parents’ subjective evaluation of training accessibility and efficacy. The questionnaires will be adapted from the study of Butti et al. (48). Questions like “I find it difficult to motivate my child for doing the training”/“I find it difficult to start the training”; or “I would suggest this training to other people I know”/“I think other people I know would enjoy doing this training” will be rated from 1 (completely disagree) to 5 (completely agree). Response will be reversed in the negative items, so that higher scores will suggest more positive evaluation/higher acceptability.

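### Acceptability is collected only at T1, so it will describe the families who attend T1 and leave out any who quit the study before it

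*Protocol article*

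**What the plan says.** The Design section of the protocol article fixes the timing: "The acceptability questionnaires will be administered only after the end of the training (T1". The same section places that visit "1 or 2 days after the end of the treatment (T1".

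The section on feasibility and acceptability of the training names the respondents and the content: "the acceptability will be assessed by asking the child/adolescent and his/her parents’ subjective evaluation of training accessibility and efficacy". Each item "will be rated from 1 (completely disagree) to 5 (completely agree", negative items are reversed, and higher scores mean higher acceptability. It mentions no questionnaire at early discontinuation.

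The same section defines feasibility separately, by "the number of patients who complete the 2-week training" and "the number of sessions completed per patient".

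The Statistical analysis section keeps in the analysis "all the participants who had completed the pre- and post-treatment evaluation sessions, even if they had not completed all the training sessions", and states that missing data will not be imputed. The section on transcutaneous stimulation foresees discontinuation for serious adverse effects, withdrawn consent or a relevant change in health.

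**The concern.** Acceptability asks how hard it was to start the training, how hard it was to motivate the child, and whether the family would recommend it. A family that leaves out of dissatisfaction would be expected to score low on such items. If the only administration is a visit that this family does not attend, its view is missing for a reason linked to the answer itself.

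This is a data-collection rule. Once the trial has run, no analysis can recover an answer that was never requested, and the plan does not impute.

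What is at stake is a descriptive result: how families regard an intensive programme of 30 hours over two weeks, which the article hopes to offer more widely. With 44 participants, a few absent families can visibly move an item percentage.

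**Working it through.** **Who is asked.** Three statements have to be read together.

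1. Design: the questionnaire is given at T1 and not at T0 or T2.
2. Statistical analysis: the analysed participants attended T0 and T1 but need not have completed every session. Attending T1 and completing training are therefore separate things, and the group asked is T1 attenders.
3. Statistical analysis: no imputation. A family absent at T1 contributes nothing to acceptability.

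**What other measures capture.** Feasibility shows how many stopped and how many sessions each child completed. Discomfort and sensation ratings are taken after every stimulation session (section on safety and tolerability measures), so early leavers contribute to those until they go. Neither records how the leavers or their parents viewed the training.

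**Size.** The article gives no dropout rate, no expected acceptability score and no threshold for it, so there is no planned figure to reproduce. From the document come only the total of 44 participants and the 1 to 5 scale. Everything else here is assumed:

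- T1 attenders average 4.2.
- Those lost before T1 would have averaged m, with m from 1.5 to 3.
- The number lost, w, runs from 0 to 8.

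Mean over all randomised = [(44 − w) × 4.2 + w × m] / 44.

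Overstatement = 4.2 − that mean = (w / 44) × (4.2 − m).

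| Lost before T1 (w) | Share of 44 | Overstatement, m = 3 | Overstatement, m = 1.5 |
|---|---|---|---|
| 0 | 0% | 0 | 0 |
| 2 | 4.5% | 2/44 × 1.2 = 0.05 | 2/44 × 2.7 = 0.12 |
| 4 | 9.1% | 4/44 × 1.2 = 0.11 | 4/44 × 2.7 = 0.25 |
| 8 | 18.2% | 8/44 × 1.2 = 0.22 | 8/44 × 2.7 = 0.49 |

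**A single item.** Suppose 90% of attenders agree with a favourable statement. The bounds over all 44 come from letting every lost family disagree, or every one agree:

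- w = 4: 0.9 × 40 = 36, so 36/44 = 82% to (36 + 4)/44 = 91%.
- w = 8: 0.9 × 36 = 32.4, so 32.4/44 = 74% to (32.4 + 8)/44 = 92%.

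The reported 90% lies near the top of both ranges, because a high agreement rate leaves more room below than above.

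**The case against.** **The word for exclusivity is about visits.** In the Design section it stands in a list of schedules, beside two questionnaires given only at T0 and T2. In that context it separates T1 from the other visits and does not forbid asking someone who stops early. That is fair. It still leaves no stated occasion on which a family absent at T1 would be asked.

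**T1 is a sensible time.** The questionnaire seeks a "subjective evaluation of training accessibility and efficacy", which needs exposure to the training. This stands as a reason for T1 as the main time point. A family leaving part-way has also had some exposure.

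**Non-completion is reported anyway.** Feasibility counts, per-session tolerability ratings and the commitment to CONSORT reporting make losses visible. That lessens the concern, but it does not supply the leavers' views of the training.

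**This is a condensed article.** The full protocol may contain an exit procedure. If it does, the point is settled. It is raised because the article states the timing rule explicitly and as the sole administration.

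**Stronger readings that do not hold.** A reader might infer that the result will be that of training completers, and that anyone who stops is never asked. The analysis-set definition contradicts this, since it expects T1 attenders who did not finish all sessions. A reader might also infer that the score can only be biased upward. The listed reasons for discontinuation include changes in health, and a child who leaves for that reason need not be a low scorer.

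**Conclusion.** The point holds in a limited form. As written, acceptability will describe families who attend T1, whether or not they finished training, and will be silent on families who leave the study before T1. The score is too favourable on the condition that the leavers found the training less acceptable than the attenders did.

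On the assumed values the overstatement is about 0.05 to 0.5 points on the 1 to 5 scale for 2 to 8 of 44 lost, and zero with no loss. Over a two-week programme the loss before T1 may well be small, but the documents give no rate. Acceptability stands apart from the primary and secondary outcomes, and the comparison of active with sham stimulation does not depend on it. This is a cheap improvement to a minor descriptive outcome.

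**What to change.** In the Design section, change the timing to: *administered at T1, or at the time of discontinuation for a participant who leaves before T1*. Report acceptability together with the number of randomised families who did not answer.

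While editing, reconcile the legend of Figure 1, which says that every measure other than the PedsQL and VABS-II is given at all time points. Taken literally, that does not fit the T1-only rule for acceptability.

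The cost is one sentence and the existing questionnaire offered to a few more families. Some who withdraw will decline, and answers given part-way reflect less exposure, so they should be identifiable in the report. The count of non-respondents is informative even where nobody answers.
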